### Study outcomes and measurement

The primary outcome will be assessed at three predefined time points: 2 weeks, 4 weeks, and 12 weeks after discharge. Secondary clinical endpoints will be evaluated at the same time points as the primary outcome. Patient-reported quality of life measures will be assessed during hospitalization, at discharge, and at 12 weeks post-discharge. Additionally, assessments of symptom relief and safety monitoring will be conducted during the hospital stay (as detailed in Table 2).

**Table 2 T2:** Summarizes the timing of enrollment, interventions, and outcome assessments.

Visit ID	V1	V2	V3	V4	V5	V6
Case Report Form (CRF)	A	B		C	D	E
	Screening	Baseline/Randomization	Discharge	Follow-up 1	Follow-up 2	End-of-Study Visit
Time from Randomization	-1-0 week	-1-0 week	0 week	2 week	4 week	12 week
Assessment Window	–	–		±3 days	±3 days	±3 days
Informed Consent	X					
Demographic Data		X				
Personal History		X				
Physical Examination		X				
Comorbidities		X				
Laboratory Tests		X				X
Concomitant Medications		X		X	X	X
Event Adjudication				X	X	X
Heart Failure Symptom Assessment (KCCQ/VAS)		X	X			X (KCCQ)
Bioelectrical Impedance Measurement		X (Daily during hospitalization, intervention group)				

The primary outcome of this study is the composite endpoint of heart failure rehospitalization and all-cause death within 3 months after discharge; the secondary outcomes include rehospitalization for heart failure within 3 months after discharge, cardiovascular death within 3 months after discharge, all-cause death within 3 months after discharge, the change of Kansas City Cardiomyopathy Questionnaire (KCCQ) quality of life score from baseline to discharge and 3 months after discharge, the dose of diuretics used during hospitalization and dyspnea and changes in overall condition at 72 h after admission (VAS scale); the safety endpoints include the incidence of acute kidney injury and hypotension during hospitalization, the incidence of electrolyte imbalance during hospitalization and follow-up period.

The time origin for the primary endpoint is defined as the date of hospital discharge. Participants will be followed for 90 days after discharge.

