#### Endpoint definitions

Heart-failure rehospitalization is defined as an unplanned hospital admission lasting ≥24 h with a primary diagnosis of heart failure, accompanied by worsening signs/symptoms of congestion and requiring intensification of HF therapy (e.g., intravenous loop diuretics and/or vasoactive therapy). Planned admissions for elective procedures without clinical deterioration are not counted as endpoint events. All-cause death is defined as death from any cause occurring within 90 days after discharge.

Hypotension is defined as a systolic blood pressure <85 mmHg during hospitalization requiring reduction in diuretic therapy or initiation of vasopressor support.

Acute kidney injury (AKI) is defined as the occurrence of any one of the following: 1) Serum creatinine increases by ≥0.3 mg/dl (≥26.5 μmol/L) within 48 h; 2) Creatinine rises to >1.5 times baseline, indicating known or presumed renal dysfunction occurring within 7 days; 3) Urine output <0.5 ml/(kg·h) for at least 6 consecutive hours.

Electrolyte disturbances: 1) Hyperkalemia is defined as any serum potassium level >5.5 mmol/L observed during hospitalization or follow-up. 2) Hypokalemia is defined as any serum potassium level <3.5 mmol/L observed during hospitalization or follow-up. 3) Hyponatremia is defined as any serum sodium level <130 mmol/L observed during hospitalization or follow-up. Hypernatremia is defined as any serum sodium level >150 mmol/L observed during hospitalization or follow-up.

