#### Event ascertainment and adjudication

Potential endpoint events will be identified through 1) in-hospital electronic medical records and discharge databases, and 2) standardized follow-up contacts at 2, 4, and 12 weeks after discharge. For hospitalizations outside the study center, participants or family members will be asked to provide discharge summaries and key supporting documents (admission/discharge notes, medication records, imaging/laboratory reports). All suspected events will be adjudicated by an independent Clinical Events Committee blinded to treatment allocation and BCM data, using prespecified definitions. Disagreements will be resolved by consensus or a third adjudicator.

After investigators submit the relevant case-report documentation, independent, blinded medical adjudicators contracted for the study will determine 3-month cardiovascular mortality, all-cause mortality, number of heart-failure hospitalizations, time to first heart-failure admission, and any associated questionnaires.

The Kansas City Cardiomyopathy Questionnaire (KCCQ) will be administered at baseline by an independent, blinded assessor on site; at the 3-month follow-up, the same instrument will be completed via telephone by an independent, blinded assessor.

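### The primary endpoint runs to day 90 after discharge, but the last scheduled contact falls on days 81 to 87, so day-90 status is never confirmed by contact

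*Protocol article*

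**What the plan says.** In the protocol article, *Study outcomes and measurement* fixes the clock and the horizon: "The time origin for the primary endpoint is defined as the date of hospital discharge", and "Participants will be followed for 90 days after discharge". *Endpoint definitions* uses the same horizon for one component: "All-cause death is defined as death from any cause occurring within 90 days after discharge". Elsewhere the article describes the primary endpoint as a 3-month outcome.

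The contact schedule is stated in weeks. *Study outcomes and measurement* says "The primary outcome will be assessed at three predefined time points: 2 weeks, 4 weeks, and 12 weeks after discharge". Table 2 gives the 12-week visit (V6) a window of 3 days either side, names it "End-of-Study Visit", and lists nothing after it. The time row of that table is headed "Time from Randomization", although the row itself places discharge at week 0.

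*Event ascertainment and adjudication* gives two sources for potential events. One is electronic records held in hospital together with discharge databases, with no cut-off date stated. The other is "standardized follow-up contacts at 2, 4, and 12 weeks after discharge". For admissions outside the study centre, participants or relatives are asked to supply the paperwork.

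**The concern.** The article gives both a 90-day horizon and a last contact that cannot reach it. This is a conflict between two stated figures, not a detail left to a fuller document.

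The consequence depends on how the last days are handled:

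- If participants without a known event are counted event-free to day 90, any event in the gap that the records do not show is missed, and the event rate is biased slightly downward.
- If they are censored at last contact, the hazard ratio stays valid, but the Kaplan–Meier curve stops short of the horizon that defines the endpoint.

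The events most exposed are deaths outside hospital and heart-failure admissions to other hospitals. Both count towards the primary composite, and admissions elsewhere are documented through the participant or family.

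**Working it through.** **Inputs.** Horizon: 90 days from discharge (*Study outcomes and measurement*; *Endpoint definitions*). Last contact: 12 weeks after discharge, 3 days either side (same section and Table 2). Planning rates by 3 months: 24.9% control and 19.9% intervention; 269 randomised per group, 242 before the attrition allowance (*Sample size*).

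**Step 1, the dates.** 12 × 7 = day 84. The window runs from 84 − 3 = day 81 to 84 + 3 = day 87. The shortfall against day 90 is 9, 6 or 3 days for contact on day 81, 84 or 87. As a share of follow-up, 3/90 = 3.3% and 9/90 = 10%. No permitted date reaches day 90.

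**Step 2, first events expected in the gap.** The documents give no hazard shape, so I assume a constant hazard in each arm: λ = −ln(1 − p)/90, with the proportion having a first event between day d and day 90 equal to exp(−λd) − (1 − p).

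- Control: λ = −ln(0.751)/90 = 0.00318 per day.
- Intervention: λ = −ln(0.801)/90 = 0.00247 per day.

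| Last contact | Control, proportion | Control, of 269 | Intervention, proportion | Intervention, of 269 | Both arms |
|---|---|---|---|---|---|
| Day 81 | 0.0218 | 5.9 | 0.0180 | 4.8 | 10.7 |
| Day 84 | 0.0145 | 3.9 | 0.0119 | 3.2 | 7.1 |
| Day 87 | 0.0072 | 1.9 | 0.0059 | 1.6 | 3.5 |

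**Step 3, scale.** Expected events by day 90 are 269 × (0.249 + 0.199) = 120.5. The gap holds 3.5/120.5 = 2.9% to 10.7/120.5 = 8.9% of them, and 7.1/120.5 = 5.9% at the scheduled day. With 242 per group, the control figures become 5.3, 3.5 and 1.7.

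**Step 4, how to read these numbers.** They count first events that occur in the gap, not events lost. Readmissions to the study hospital should still appear in its records, so the number lost is smaller by an amount the documents do not give. The day-81 row requires everyone to be contacted on the earliest permitted day. If risk is concentrated soon after discharge, all rows shrink.

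**The case against.** The strongest reply is that the gap is a few days long, identical in both arms, and partly covered by a records search that is not tied to visit dates. The analysis in *Statistical analysis* is time to first event with a log-rank test and a Cox model, and that comparison remains valid if participants are censored when last contacted. The date of the records extraction and the censoring rule are matters an article may leave to the full protocol or analysis plan. All of this stands and limits the point's weight. It does not remove the conflict between the two stated figures.

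Four stronger readings are tempting but not supported:

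- *That outside events after the last contact are certainly lost.* The article does not say whether the discharge databases extend beyond the study hospital. They may be missed; no more can be said.
- *That the primary analysis fails because a 90-day rate cannot be estimated.* The stated effect measure is a hazard ratio, not a 90-day proportion. Censoring at last contact costs a few events and the last days of the curve.
- *That the last contact comes earlier still, by the length of stay, because of the Table 2 heading.* The same row places discharge at week 0, and the text counts visits from discharge. The heading is a wrong label.
- *That cutting the horizon to the earliest permitted contact would be an equivalent repair.* Day 81 is less than 12 weeks and would redefine an endpoint stated as 3 months.

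**Conclusion.** The point holds as an inconsistency in the primary endpoint's follow-up: the horizon is day 90, and scheduled contact ends 3 to 9 days earlier. In that interval ascertainment relies on records and databases alone. Under a constant hazard at the planning rates, about 2 to 6 control participants of 269 (about 4 at day 84), or 3.5 to 10.7 participants across both arms, would have a first event there. These are upper bounds on events lost. Any bias in the event rate is small and downward, and arises only if participants are counted event-free to day 90. Nothing in the documents points to a difference between arms. The point deserves correction because it concerns the primary endpoint and is cheap to repair. It does not threaten the validity of the treatment comparison.

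**What to change.** Schedule the final contact on or after day 90 from discharge with a one-sided window, for example days 90 to 97. Ask then about all events up to and including day 90, and censor at last contact where that is earlier. Use the 90-day horizon consistently wherever the text now alternates between 12 weeks, 3 months and 90 days.

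The abstract says recruitment is under way, so some participants may already have completed V6. For them, either make one brief additional status call or censor at the V6 date.

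Relabel the time row of Table 2 as time from discharge. The data capture system generates visit dates and windows automatically (*Data collection and management*), so the label should match the intended origin.

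The cost is a minor amendment, which under *Ethics approval* and *Protocol amendments* needs ethics-committee approval before use, a changed visit window in the data capture system, and a final call a few days later for each participant.

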#### Endpoint definitions

Heart-failure rehospitalization is defined as an unplanned hospital admission lasting ≥24 h with a primary diagnosis of heart failure, accompanied by worsening signs/symptoms of congestion and requiring intensification of HF therapy (e.g., intravenous loop diuretics and/or vasoactive therapy). Planned admissions for elective procedures without clinical deterioration are not counted as endpoint events. All-cause death is defined as death from any cause occurring within 90 days after discharge.

Hypotension is defined as a systolic blood pressure <85 mmHg during hospitalization requiring reduction in diuretic therapy or initiation of vasopressor support.

Acute kidney injury (AKI) is defined as the occurrence of any one of the following: 1) Serum creatinine increases by ≥0.3 mg/dl (≥26.5 μmol/L) within 48 h; 2) Creatinine rises to >1.5 times baseline, indicating known or presumed renal dysfunction occurring within 7 days; 3) Urine output <0.5 ml/(kg·h) for at least 6 consecutive hours.

Electrolyte disturbances: 1) Hyperkalemia is defined as any serum potassium level >5.5 mmol/L observed during hospitalization or follow-up. 2) Hypokalemia is defined as any serum potassium level <3.5 mmol/L observed during hospitalization or follow-up. 3) Hyponatremia is defined as any serum sodium level <130 mmol/L observed during hospitalization or follow-up. Hypernatremia is defined as any serum sodium level >150 mmol/L observed during hospitalization or follow-up.

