### Blinding

This is an open-label trial with blinded endpoint adjudication. An independent Clinical Events Committee (CEC), whose members are blinded to treatment allocation, patient identity, and all fluid load data, will adjudicate all potential primary and secondary endpoint events according to pre-specified, standardized definitions.

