BCM measurements will be performed using the Body Composition Monitor (Fresenius Medical Care, Germany) with standard wrist-to-ankle electrode placement according to the manufacturer's instructions. Measurements will be conducted once daily in the morning before intravenous diuretic administration. Participants will rest in a supine position for at least 5–10 min prior to measurement and will be instructed to refrain from excessive fluid intake for at least 2 h before the assessment.Overhydration (OH) values will be automatically calculated using the device's validated algorithm. Detailed measurement procedures are provided in Supplementary File S1. If a BCM measurement is not feasible on a given day, the reason must be documented, and volume management for that day will revert to protocol-defined clinical assessment criteria.

Safety triggers for de-escalation or interruption of diuretic therapy will include hypotension, worsening renal function, or clinically significant electrolyte abnormalities. In such cases, treating physicians will be allowed to deviate from the algorithm to ensure patient safety. All recommended adjustments and actual treatments will be prospectively documented, and protocol deviations will be recorded for subsequent per-protocol and sensitivity analyses.

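### The hypotension endpoint counts a low pressure only if unblinded physicians act on it, partly through the randomised treatment; electrolyte events can predate randomisation, and low urine output alone can define AKI

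*Protocol article*

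**What the plan says.** All three safety endpoints are defined in the protocol article under Endpoint definitions.

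- **Hypotension:** "Hypotension is defined as a systolic blood pressure <85 mmHg during hospitalization requiring reduction in diuretic therapy or initiation of vasopressor support". A pressure below the threshold is not an event unless one of the two actions follows.
- **AKI:** any one of three criteria is enough. Two rest on creatinine: "Serum creatinine increases by ≥0.3 mg/dl (≥26.5 μmol/L) within 48 h" and "Creatinine rises to >1.5 times baseline" (within 7 days). The third is "Urine output <0.5 ml/(kg·h) for at least 6 consecutive hours".
- **Electrolytes:** each disturbance is a single value beyond a limit. For example, "Hypokalemia is defined as any serum potassium level <3.5 mmol/L observed during hospitalization or follow-up", and hyponatremia is "any serum sodium level <130 mmol/L observed during hospitalization or follow-up". No condition requires the value to be new or to follow randomisation.

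Other sections bear on how these rules work:

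- The Run-in phase section allows up to 24 h between admission and randomisation.
- Intervention strategy ties diuretic increases, reductions and withholding to the daily OH value in the BCM arm only. It adds: "Safety triggers for de-escalation or interruption of diuretic therapy will include hypotension, worsening renal function, or clinically significant electrolyte abnormalities". Control strategy has no matching list and leaves titration to the physician.
- Strengths and limitations states that the clinical team cannot be blinded.
- Statistical analysis compares the safety endpoints as proportions by χ² or Fisher's exact test.
- Blinding says the events committee "will adjudicate all potential primary and secondary endpoint events according to pre-specified, standardized definitions". Event ascertainment and adjudication sends every suspected event to that blinded committee. Table 2 marks adjudication only at the three visits after discharge.

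**The concern.** The safety question is whether guided diuresis causes hypotension, renal injury or electrolyte disturbance. The same three signals are named for committee review under Interim analyses and stopping guidance. An outcome definition for that purpose should not depend on the treatment being compared, and it should count what happens after randomisation.

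The hypotension rule fails the first test. One of its two qualifying actions is a change in the randomised treatment, made by physicians who know the arm. The urine-output route to AKI raises a milder form of the problem, because diuretic dose acts on urine output directly. The electrolyte rule fails the second test, since an abnormal admission value counts as an event. In a harm comparison, mixing in prevalent abnormalities pulls the result towards no difference and so towards reassurance.

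**Working it through.** The document gives no safety event rates, so there is no stated figure to reproduce. Every rate below is an assumption chosen to show size. The 269 per arm is from Sample size. Rejection probabilities are for a two-sided 5% comparison of two proportions (normal approximation).

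**1. Hypotension.** Counted rate = P(SBP <85) × P(qualifying action given SBP <85). Take a true rate of 10% in both arms.

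- Action in 80% vs 50%: 0.10 × 0.80 = 8.0%; 0.10 × 0.50 = 5.0%; ratio 1.60.
- Action in 50% vs 80%: 5.0% vs 8.0%; ratio 0.625.
- Action in 70% vs 50%: 7.0% vs 5.0%; ratio 1.40.
- Action in 60% in both: 6.0% vs 6.0%; ratio 1.00.

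The true rate cancels from the ratio but affects how often a false difference reaches significance. At true rates of 5%, 10% and 15%, that chance is about 10%, 16% and 23% for 70% vs 50%, and about 16%, 29% and 42% for 80% vs 50%, against a nominal 5%.

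The text supports mechanisms in both directions. Written safety triggers in the BCM arm could make action on a low pressure more frequent there. But a patient in that arm whose diuretic is already withheld because of OH has nothing left to reduce and can qualify only through a vasopressor.

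**2. Electrolytes.** Counted rate = b + (1 − b) × new-onset rate, where b is the prevalence before randomisation, equal in both arms in expectation. Take new-onset rates of 15% vs 10%.

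| b | Counted rates | Ratio | Power, 269 per arm |
|---|---|---|---|
| 0% | 15.0% vs 10.0% | 1.50 | 42% |
| 5% | 19.25% vs 14.5% | 1.33 | 31% |
| 10% | 23.5% vs 19.0% | 1.24 | 25% |
| 20% | 32.0% vs 28.0% | 1.14 | 17% |
| 30% | 40.5% vs 37.0% | 1.09 | 13% |

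**3. AKI.** Counted rate = c + (1 − c) × u, where c is creatinine-based AKI and u is the urine-output-only rate among the rest.

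- c = 15% in both, u = 10% in both: 23.5% vs 23.5%; ratio 1.00.
- c = 15% in both, u = 5% vs 10%: 0.15 + 0.85 × 0.05 = 19.25%; 0.15 + 0.85 × 0.10 = 23.5%; ratio 0.82. With the arms swapped, 23.5/19.25 = 1.22.
- c = 20% vs 15% (ratio 1.33), u = 5% vs 10%: 0.20 + 0.80 × 0.05 = 24.0%; 0.15 + 0.85 × 0.10 = 23.5%; ratio 1.02.

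A difference in the creatinine criteria can therefore disappear in the combined endpoint. Whether it would depends on u in each arm, which the document does not give.

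**4. Adjudication.** Blinding names primary and secondary endpoint events. Event ascertainment and adjudication covers all suspected events and draws on in-hospital records. Table 2 schedules adjudication only after discharge, whereas hypotension and AKI are in-hospital endpoints. The three places do not agree on whether these events are reviewed.

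**The case against.** The strongest reply is that the action clause is a filter for clinical significance. The vasopressor route is not specific to either arm. The safety-trigger text ends by permitting physicians to depart from the algorithm, which is discretion much like that in the control arm, and both arms are treated to heart-failure guidelines. Safety outcomes are outside the primary test, and Statistical analysis says they will be interpreted cautiously. For electrolytes, Table 1 excludes patients with repeated disturbances in the past year, Table 2 has baseline laboratory tests, and a treatment-emergent rule might sit in an analysis plan that is not shown.

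Much of this stands, and it limits what can be claimed. A reader might infer any of the following, and the document supports none of them:

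- **Hypotension will be over-reported in the BCM arm, or hypotension and AKI are biased in opposite directions.** The algorithm both intensifies and withholds diuretics, controls are titrated too, and no action rates are given.
- **The AKI definition as a whole depends on treatment.** Only the urine-output criterion is directly exposed. It can add cases but cannot remove one that meets a creatinine criterion.
- **Pre-randomisation electrolyte values favour one arm.** Randomisation balances them in expectation; the harm is dilution.
- **Safety events escape blinded review.** One section sends all suspected events to the blinded committee, so coverage is inconsistent rather than plainly absent.

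The reply does not remove the core. A significance filter operated by unblinded physicians through the randomised treatment is still part of the outcome, and blinded adjudication comes after the qualifying action. The past-year exclusion limits abnormal admission values without removing them. The electrolyte counting rule is written out in the article, and followed as written it includes values from before randomisation.

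**Conclusion.** The point holds in a limited form. The hypotension definition is the main weakness: with no true difference, the reported ratio could be 1.60, 1.00 or 0.625 depending on assumed action rates, and the document gives no basis for choosing among them. The electrolyte rule dilutes a real difference. On assumed new-onset rates of 15% vs 10%, the ratio of 1.50 falls to between 1.33 and 1.09 as baseline prevalence goes from 5% to 30%. The urine-output criterion can blur the AKI comparison, while the creatinine criteria carry no treatment condition. The scope of blinded adjudication needs reconciling. None of this touches the primary efficacy test, and the numerical thresholds are not in question.

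**What to change.** For the between-arm safety comparison:

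- **Hypotension:** count SBP <85 mmHg recorded after randomisation, irrespective of the action taken, and report the action as a second tier.
- **Electrolytes:** count a value only when it is new or worsened after randomisation relative to the baseline laboratory tests, and state what counts as worsened.
- **AKI:** report creatinine-based AKI separately from AKI met by urine output alone.
- **Adjudication:** make Blinding, Event ascertainment and adjudication, and Table 2 agree on whether the blinded committee covers in-hospital safety events.

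The cost is endpoint wording and programming. Thresholds and patient management do not change. Event counts will differ from those under the published definitions, which can be kept as a sensitivity listing. Recruitment is under way, so the change should be made before any comparison by arm is seen.
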